### Statistical analysis

Baseline group variables will be summarized using the mean and standard deviation for continuous measures and percentages for categorical measures. Independent *t*-tests (*P* <0.05, two-tailed) or the appropriate nonparametric test will be used to compare between-group differences in baseline characteristics (Table 1). Parametric test assumptions will be analyzed for all continuous variables by visual inspection of histograms, use of skewness score within double the standard error of skewness criteria, and Levene’s test for homogeneity of the variance. A repeated measures analysis of variance will be used to compare group differences in the FAAM, NPRS, EQ-5D™, and number of office visits associated with treatment at each time point. Results will be reported as the group mean, mean difference between groups, 95% confidence intervals, f-value, *P* value, power, and effect size. The χ^2^ test will be used to compare GROC scores between groups at each time point and results will be reported as the χ^2^ value, *P* value, and the frequency per category. The types of treatment based on Current Procedural Terminology and Healthcare Common Procedure Coding System codes provided per group will be reported as percentages. Analysis of covariance will be used if any group differences are observed in participant characteristics. Intention-to-treat analysis will be performed by comparing the complete case analysis to multiple imputation analysis. Multiple imputed data sets will be generated using the Multivariate Imputation by Chained Equations algorithm with SPSS 19.0 for Windows (SPSS Inc., Chicago, IL, USA). Multinomial logistic regression will be used to obtain pooled regression estimates from the data sets that will be used for analysis. Post-randomization exclusion of included participants that did not meet eligibility criteria or that did not receive intervention will be considered for exclusion of the analysis by an independent, blinded adjudication committee that will evaluate all randomized participants [57]. Any crossovers will be analyzed in the original group to which they were assigned. A separate analysis excluding crossovers will be performed.

Participant expectations and preferences for ePT or uPOD will be categorized into three categories; matched, unmatched, and neutral. Participants will be labelled ‘matched’ if they are allocated to a group for which they have expressed a higher expectation of benefit. A higher expectation will be denoted by comparison of visual analog ratings between the groups (ePT and uPOD; Additional file 1). Unmatched participants will be those who are allocated to the treatment group for which they have a lower expectation of benefit. Neutral participants will be those who indicate the same level of expectation for both treatments. Similar categorizations will be made for participant preference based upon their response to the treatment preference question (Additional file 1). General expectations of improvement will be dichotomized into met or unmet based upon rankings at the 6-week, 6-month, and 1-year follow-up relative to baseline rankings. Participants that demonstrate 6-week, 6-month, and 1-year ranks equal to or higher than baseline will be considered to have met their global expectations of improvement. Participants that demonstrate rankings below baseline expectations will be considered to have unmet global expectations of improvement. A χ^2^ test of independence will be used to compare the proportions of individuals with matched/unmatched/neutral expectations or preferences to global expectations (met or unmet). In addition, differences in expectation and preference categories will be analyzed relative to treatment success using a χ^2^ test of independence. Treatment success will be determined by the GROC at each period with success defined as a GROC of +5, “a great deal better”, or greater.

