**Methods:**

A parallel-group, block-randomized clinical trial will compare ePT and uPOD. Both groups will be seen initially by a podiatrist before allocation to a group that will receive physical therapy intervention consisting primarily of manual therapy, exercise, and modalities, or podiatric care consisting primarily of a stretching handout, medication, injections, and orthotics. Treatment in each group will be directed by practice guidelines and a procedural manual, yet the specific intervention for each participant will be selected by the treating provider. Between-group differences in the Foot and Ankle Ability Measure 6 months following the initial visit will be the primary outcome collected by an independent investigator. In addition, differences in the European Quality of Life – Five Dimensions, Numeric Pain Rating Scale, Global Rating of Change (GROC), health-related costs, and cost-effectiveness at 6 weeks, 6 months, and 1 year will be compared between groups. The association between successful outcomes based on GROC score and participant expectations of recovery generally, and specific to physical therapy and podiatry treatment, will also be analyzed.

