### Specific aims

Aim 1: Compare the difference in outcome between ePT versus uPOD. The null hypothesis that no difference in the Foot and Ankle Ability Measure (FAAM) between ePT and uPOD in individuals with PHP at the 6-month follow-up will be tested using a randomized clinical trial.

Aim 2: Compare the difference in secondary outcome measures using the 3-item (average, worst, least) numeric pain rating scale (NPRS), and global rating of change (GROC) scale. These measures will be taken concurrently with the FAAM in the randomized clinical trial to test the null hypothesis that there is no difference in NPRS and GROC between ePT and uPOD.

Aim 3: Compare the cost-effectiveness of ePT versus uPOD. Costs and quality of life measures will be captured concurrently in the randomized clinical trial to calculate incremental cost-effectiveness ratios and test the null hypothesis that there is no difference in cost-effectiveness between ePT and uPOD.

Aims 1 and 2 will be the focus of this paper although Aim 3 will also be considered in the planning of this project and is included here for clarity of the entire project’s scope. The procedures to accomplish Aim 3 will be outlined in a subsequent publication.

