The number of participants for this study is based on the power needed to detect between-group differences in the primary outcome measure, the FAAM, at 6 months. In the absence of research comparing physical therapy and podiatry interventions or podiatry interventions using the FAAM as an outcome measure, sample size calculations are based on achieving a clinically meaningful difference between the groups and details from a recent clinical trial by Cleland et al. [10] that used similar methods to this investigation. Sample size estimate was made using G*Power 3.1.5 based on detecting a difference between groups greater than the minimal clinically important difference (MCID) (i.e., 9 point change) of the FAAM at 6 months with an alpha level of 0.05, 80% power, and pooled sample variance of 14.5 from Cleland et al. [10,30,32]. This resulted in an effect size of 0.62 and 42 participants needed per group. To account for participants who drop-in or drop-out of treatment, in addition to the possibility of some participants not returning the FAAM questionnaire, the sample will be increased by 33% resulting in 56 participants per group. The focus, and consequently the power analysis of this investigation is on functional outcome (based on FAAM scores) and therefore may result in underpowered analysis of secondary variables.

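### The primary question is the 6-month FAAM difference, but the stated repeated measures ANOVA does not name that contrast as the primary test, and baseline adjustment depends on observed imbalance

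*Protocol article*

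**What the plan says.** Three places in the protocol article fix the primary question at one time point.

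- Abstract, Methods: "Between-group differences in the Foot and Ankle Ability Measure 6 months following the initial visit will be the primary outcome".
- Specific aims, Aim 1: the null hypothesis of "no difference in the Foot and Ankle Ability Measure (FAAM) between ePT and uPOD in individuals with PHP at the 6-month follow-up will be tested".
- Participants, sample size: the number is "based on the power needed to detect between-group differences in the primary outcome measure, the FAAM, at 6 months". It is computed "with an alpha level of 0.05, 80% power, and pooled sample variance of 14.5", giving 42 per group, raised to 56.

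The Statistical analysis section states the method: "A repeated measures analysis of variance will be used to compare group differences in the FAAM, NPRS, EQ-5D™, and number of office visits". The sentence goes on to place the comparison at each time point. The results to be reported include group means, mean differences, 95% confidence intervals, an F-value and a P value. The section does not say which term or contrast is the primary test, or whether baseline is a level of the time factor.

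The same section also plans the following:

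- Baseline tests: "Independent *t*-tests (*P* <0.05, two-tailed) or the appropriate nonparametric test will be used to compare between-group differences in baseline characteristics". FAAM is among the Table 1 characteristics.
- Analysis of covariance, if any group difference in participant characteristics is observed. The covariates are not named.
- A complete-case analysis set against multiple imputation by chained equations, with neither called primary.

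**The concern.** A repeated measures ANOVA with a group factor and a time factor yields two F-tests that involve group. The main effect concerns the difference averaged over visits. The interaction asks whether the difference varies between visits. Neither is the null of no difference at 6 months. If the deciding term is left open, it can be picked once the data are seen. A significant F could then be reported for Aim 1 with no 6-month difference, or a real 6-month difference could be missed.

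The conditional covariance rule is a second weakness. It makes the primary model depend on significance tests of randomised baseline variables. If the variable that differs is the one adjusted for, baseline FAAM enters only when FAAM itself differs, which under randomisation happens in about 5% of trials at the 0.05 level. The precision available from a measurement already collected is then usually lost.

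The third is missing data. In a complete-case run of a classical repeated measures ANOVA, one missing 6-week or 1-year form discards an observed 6-month score.

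**Working it through.** **1. The plan's own figure.** Target difference 9 and spread 14.5 (Participants). The text calls 14.5 a variance, but the stated effect size follows only if it is an SD: 9/14.5 = 0.62. For a two-sided, two-sample t-test with 42 per group, the noncentrality is 0.62 × √(42/2) = 2.84 on 82 df, and power is 0.802. With 41 per group it is 0.792, so 42 is reproduced. The sidedness of this test is not stated; one-sided would give 33. Inflation: 42 × 1.33 = 55.9, i.e. 56. The trial is sized for an unadjusted comparison at a single time point.

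**2. What the omnibus tests detect.** The documents give no correlation between visits. I assume equal correlation ρ = 0.3, 0.5 or 0.7, SD σ = 14.5 at each visit, n = 42 per arm with complete data, and four levels of time (baseline, 6 weeks, 6 months, 1 year). Let δ_j be the group difference at visit j and δ̄ its mean.

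- Interaction: λ = (n/2) Σ(δ_j − δ̄)² / [σ²(1 − ρ)], on 3 and 3 × 82 = 246 df.
- Main effect: d = δ̄ / √[σ²(1 + 3ρ)/4], two-sample t-test on 82 df.

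*Effect of 9 points at 6 weeks only.* Σ(δ_j − δ̄)² = 81 × 3/4 = 60.75. At ρ = 0.5, λ = 21 × 60.75 / (210.25 × 0.5) = 12.14.

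*Effects of 3, 9 and 5 points at 6 weeks, 6 months and 1 year.* δ̄ = 17/4 = 4.25. At ρ = 0.5, d = 4.25/11.46 = 0.371.

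| Rejection probability | ρ = 0.3 | ρ = 0.5 | ρ = 0.7 |
|---|---|---|---|
| 9 at 6 weeks only: interaction | 69% | 84% | 97% |
| 9 at 6 weeks only: 6-month contrast | 5% | 5% | 5% |
| 3/9/5: main effect | 49% | 39% | 33% |
| 3/9/5: interaction | 52% | 68% | 90% |
| 3/9/5: 6-month contrast, unadjusted | 80% | 80% | 80% |

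*Sensitivity to the time factor.* With the three follow-ups only, the 6-weeks-only interaction still rejects in 69/84/97%. For 3/9/5 the main effect has 68/58/51% power and the interaction 28/38/59%.

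*Sensitivity to the profile.* With 9 points at every follow-up and four visits, the main effect has 86/76/67% power and the interaction 69/84/97%.

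**3. Adjusting for baseline FAAM.** The residual SD is 14.5 × √(1 − ρ²) = 13.83 / 12.56 / 10.36, so d = 0.651 / 0.717 / 0.869. With 42 per arm, power for 9 points at 6 months is 84% / 90% / 98%, against 80% unadjusted.

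**4. Complete-case loss.** The documents give no missingness rate by visit. I assume a fraction q missing independently at each of the three follow-ups. All-visit completers per arm are 56(1 − q)³; participants with a 6-month score are 56(1 − q). Power is for the unadjusted 6-month comparison.

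| q | Complete at all visits (power) | With 6-month score (power) |
|---|---|---|
| 5% | 48 (85%) | 53 (89%) |
| 10% | 41 (79%) | 50 (87%) |
| 15% | 34 (71%) | 48 (85%) |

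Completers fall below 42 once q exceeds 1 − (42/56)^(1/3) = 9.1%.

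**The case against.** A reader might infer three stronger things, and the document supports none of them.

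*That the trial will test the wrong hypothesis.* The analysis sentence places the comparison at each time point, and mean differences with confidence intervals are promised. Read with Aim 1, a 6-month contrast from the model is a natural reading. Nothing says that an omnibus F decides the trial. What stands is that no contrast is designated, while the reporting list includes an F-value without saying for which term.

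*That there is no baseline adjustment.* Analysis of covariance is planned, and FAAM is among the characteristics tested. What stands is that adjustment is conditional on the observed data.

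*That anyone missing a visit is lost.* Multiple imputation is planned, and under it a missing 6-week or 1-year form does not remove a 6-month score. The losses above apply only to the complete-case run, and at 10% missingness the shortfall against 42 is one participant per arm. What stands is that neither result is named primary.

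The profiles are also chosen to separate the hypotheses. If the effect is sustained, the four-visit omnibus tests perform much closer to the 6-month comparison, and at ρ = 0.7 the interaction exceeds the unadjusted comparison in power under the 3/9/5 profile, though it answers another question. Correction for sphericity and the choice of a mixed model are details an article may leave to a fuller plan, so I make no point of them. That fuller plan might also name the contrast. But the article does choose a primary method and a covariate rule, and both can be judged as stated.

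**Conclusion.** The concern holds in limited form. The primary hypothesis and sample size are for FAAM at 6 months; the stated analysis does not tie its primary test to that time point, and it lets observed baseline differences decide whether to adjust. The omnibus terms are not substitutes: they can reject often with no 6-month effect (69 to 97% in the 6-weeks-only case), or have far less power than the 6-month comparison (main effect 33 to 49% against 80% in the 3/9/5 case). These sizes rest on assumed equal correlations of 0.3 to 0.7, SD 14.5, 42 per arm, the stated effect profiles and, for the main-effect figure, baseline as a level of time. They show what an undesignated term could do, not what the trial will do. The complete-case loss depends on assumed independent missingness and concerns only that run. The gain from prespecified adjustment, from 80% to about 84 to 98% power, depends on the baseline to 6-month correlation.

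**What to change.** State one primary test: the between-group difference in FAAM ADL at 6 months, adjusted for baseline FAAM regardless of observed imbalance. Take it from an analysis of covariance of the 6-month score, or from a mixed model for repeated measures using all available visits with a group-by-visit term. Make the 6-week and 1-year contrasts secondary. Drop the rule that brings in covariates only when a baseline difference is observed. Name one missing-data approach as primary and the other as a sensitivity analysis.

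The cost is a rewording of the Statistical analysis section, made before outcomes are analysed by group. Baseline FAAM is already collected, so no data or participants are added, and 42 analysed per arm remains enough.

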#### Secondary outcome measures

A 3-item, 0–10 (0 = no pain, 10 = worst imaginable pain), NPRS will be used to assess average pain in addition the lowest and highest levels of pain in the past week. The average of the three ratings will be used to represent overall pain intensity. The 3-item NPRS has demonstrated test-retest reliability of 0.61, and an MCID of 2 points [33]. The GROC scale will be used to assess participant-reported improvement. The GROC is a single question item that includes 15 ranks for global improvement from −7 (a very great deal worse) to 0 (about the same) to +7 (a very great deal better) [34]. Scores of +5 have previously been used as an indicator of clinical success [10,35]. Overall health status will be measured by the European Quality of Life-Five Dimensions (EQ-5D™)*.* The EQ-5D™ is a general measure of health-related quality of life that includes five items related to mobility, self-care, usual activities, pain/discomfort, and anxiety/depression [36]. Index scores from the United States general population will be applied to the EQ-5D™ to calculate the quality-adjusted life year, where 0.0 = death and 1.0 = perfect health [37].

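### The 15-rank ordinal GROC is to be compared between arms with a plain chi-square test, which ignores the ordering; an ordinal method would use the same data with more power

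*Protocol article*

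**What the plan says.** The Secondary outcome measures section defines the scale: "The GROC is a single question item that includes 15 ranks for global improvement", running from −7 through 0 to +7. It adds that +5 has been used before as a marker of clinical success. Aim 2 names the GROC, with the pain rating, as an outcome with its own null hypothesis of no difference between arms.

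The Statistical analysis section fixes the between-arm test: a chi-square "test will be used to compare GROC scores between groups at each time point and results will be reported as the" chi-square value, then the P "value, and the frequency per category". It mentions no collapsing of ranks and no rank, trend or exact test. The preceding sentence promises mean differences, 95% confidence intervals and effect sizes for the outcomes analysed by repeated measures. No such estimate is promised for the GROC.

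A cut-off appears later in the same section, where expectations and preferences are related to outcome: "Treatment success will be determined by the GROC at each period with success defined as a GROC of +5" or greater.

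**The concern.** A Pearson chi-square statistic keeps the same value if the 15 ranks are put in any other order. It therefore discards the feature that makes the GROC a measure of improvement, and it spreads its sensitivity over every pattern of difference, including patterns that are not benefit. With 15 columns and 42 to 56 participants per arm the table is also thin, so the large-sample approximation is strained.

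What is at stake is the between-arm result for one of the two outcomes named in Aim 2. A real shift in perceived improvement could be reported as non-significant because of the test. The planned output would also contain no estimate of its size with a confidence interval.

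**Working it through.** **Inputs from the article.** The GROC has 15 ordered ranks. The Participants section gives the difference to detect ("i.e., 9 point change) of the FAAM at 6 months"), the other settings ("an alpha level of 0.05, 80% power, and pooled sample variance of 14.5") and the result: "This resulted in an effect size of 0.62 and 42 participants needed per group". A 33% increase then gives 56 per group.

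**Reproducing the stated sample size.** 9/14.5 = 0.62, so the 14.5 works only as a standard deviation. A two-sided t-test (sidedness assumed) at alpha 0.05 and 80% power needs 41.8, so 42 per group, with power 0.802 at 42. 42 × 1.33 = 55.9, so 56. Both stated figures reproduce. They concern the FAAM; no GROC power is stated.

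**Expected counts.** With equal arms and all ranks used, the mean expected count per cell is n per arm / 15:
- 42/15 = 2.8
- 56/15 = 3.7
- a mean of 5 would need 5 × 15 = 75 per arm.

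**Analytic power.** Take noncentrality n·d²/2 with d = 0.62, and compare a 14-df test with a 1-df test aimed at the shift:
- n = 42: 42 × 0.3844/2 = 8.07; power 0.378 against 0.811; loss 1 − 0.378/0.811 = 53%.
- n = 56: 56 × 0.3844/2 = 10.76; power 0.510 against 0.907; loss 1 − 0.510/0.907 = 44%.

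**Simulation.** This allows for sparse cells and for empty ranks, which reduce the degrees of freedom. Assumptions: a latent normal GROC cut at the 15 ranks, or uniform ranks in the control arm; a shift of 0.62 SD borrowed from the FAAM; 4000 runs per scenario (Monte Carlo standard error at most √(0.25/4000) = 0.8 percentage points). Tests: Pearson chi-square on the occupied ranks (χ²), tie-corrected Mann–Whitney (MW), and a 2×2 chi-square at +5 or more. Loss = 1 − power/power of MW.

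| Control mean, SD (assumed) | Mean ranks in use, 42/arm | 42/arm: χ² / MW / +5 | Loss: χ², +5 | 56/arm: χ² / MW / +5 | Loss: χ², +5 |
|---|---|---|---|---|---|
| 0, 4 | 14.6 | 0.244 / 0.773 / 0.504 | 68%, 35% | 0.384 / 0.877 / 0.626 | 56%, 29% |
| 2, 3 | 12.1 | 0.282 / 0.772 / 0.575 | 63%, 26% | 0.418 / 0.882 / 0.710 | 53%, 20% |
| 3, 3 | 11.0 | 0.308 / 0.771 / 0.634 | 60%, 18% | 0.445 / 0.880 / 0.729 | 49%, 17% |
| 4, 3 | 10.0 | 0.305 / 0.763 / 0.643 | 60%, 16% | 0.436 / 0.867 / 0.721 | 50%, 17% |
| 4, 2 | 8.2 | 0.370 / 0.760 / 0.661 | 51%, 13% | 0.536 / 0.883 / 0.731 | 39%, 17% |
| 5, 2 | 7.2 | 0.390 / 0.740 / 0.556 | 47%, 25% | 0.532 / 0.860 / 0.693 | 38%, 19% |
| Uniform | 14.9 | 0.272 / 0.775 / 0.570 | 65%, 26% | 0.422 / 0.896 / 0.721 | 53%, 20% |

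Over these distributions, with and without a shift, 41–95% of occupied ranks had an expected count below 5 at 42 per arm, and 34–79% at 56. With no true difference the chi-square on ranks rejected in about 3–4% of runs, below the nominal 5%. A repeat simulation at the same shift agreed closely: chi-square 0.25–0.38 against 0.74–0.78 for Mann–Whitney at 42 per arm, and 0.37–0.55 against 0.86–0.89 at 56, where the loss was 36–58%.

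**The case against.** **The table may be 2×2.** The article does not say that the categories are the 15 raw ranks. It mentions +5 when it defines the outcome and uses that cut later with a chi-square test. Under this reading there is no sparse-cell problem and the loss falls to about 13–35%. The reading is possible but less literal: the test is applied to GROC scores with a frequency per category, and the success cut is attached to the expectation and preference analysis. If the dichotomy was intended, the between-arm sentence should say so.

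**The power figures are not the trial's.** This stands. The article gives no GROC distribution or effect, the 0.62 is borrowed from the FAAM, and a pure location shift favours a rank test. If the arms differed in spread, or through a subgroup of non-responders, the gap would differ.

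**Low power for secondary outcomes is already admitted.** It is, in general terms, because the trial is sized on the FAAM. That does not account for a further loss from the choice of test.

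**Stronger readings that the article does not support.**
- A reader might infer that the test always loses more than half the power. It does so in six of the seven assumed settings at 42 per arm, but at 56 per arm the loss falls on both sides of one half.
- A reader might fear that thin cells inflate false positives. The simulated error rate is below 5%.
- A reader might say that a significant result would have no direction. The reported frequencies would show it, although without an effect estimate or interval.

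**Conclusion.** The point holds in qualified form. The article names a test that ignores the ordering of a 15-rank scale and names no ordinal alternative. Read literally, the test uses up to 14 degrees of freedom, leaves many expected counts below 5, and is conservative. Its power loss against an ordinal test is roughly 35–70%, larger at 42 than at 56 per arm and larger when more ranks are in use. On the dichotomy reading it is about 13–35%. That the test ignores order follows from the text alone. The size of the loss rests on assumed GROC distributions and a 0.62 SD shift. The GROC is a secondary outcome, so the FAAM conclusion does not depend on this point.

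**What to change.** In the Statistical analysis section, replace the chi-square sentence for the between-arm GROC comparison:
- Compare the GROC ranks between arms at each time point with an ordinal method: Mann–Whitney, or a proportional odds model reporting an odds ratio with 95% CI.
- Report the difference between arms in the proportion with a GROC of +5 or more, with 95% CI, using the success definition already in that section.
- Keep the category frequencies as description only.

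The cost is a change of wording. The data, visits and sample size stay the same.

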### Intervention

All patients will attend one visit with a podiatrist where the podiatrist will perform an evaluation and provide intervention based upon usual practice patterns. After this visit, the patient will be invited to participate in the study and undergo a baseline examination that will collect data on variables indicated by Table 1. A member of the office staff will randomize group assignment using random block sizes of 4 and 6, and concealed envelopes containing group assignment to ePT or uPOD (Figure 1).

**Table 1 T1:** Baseline measures of participant characteristics

**Characteristic**	**ePT**	**uPOD**
Age (years)		
Sex		
Height (cm)		
Weight (kg)		
BMI (kg/m^2^)		
Bilateral symptoms (%)		
Prior history of PHP (yes/no)		
Duration of symptoms (days)		
Foot Posture Index [38]		
Number of hours on feet/week		
NPRS		
FAAM		
EQ-5D™		
Healthcare resource use (US dollars)*		
General recovery expectation^†^		
Expectation for physical therapy^‡^		
Expectation for podiatry^‡^		
Treatment Preference (%):		
Neutral		
Physical Therapy		
Podiatry		

*Data derived from a participant-reported questionnaire. ^†^Measured by rating expected recovery according to the GROC scale [34]. ^‡^As measured on a 0–10 visual analog scale where 0 = not helpful and 10 = extremely helpful relative to plantar heel pain. BMI: Body mass index; ePT: Early physical therapy intervention; EQ-5D™: European Quality of Life-Five Dimensions; FAAM: Foot and Ankle Ability Measure; NPRS: Numeric pain rating scale; PHP: Plantar heel pain; uPOD: Usual podiatric care.

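### Covariate adjustment depends on whether baseline differences are observed, so chance influences whether the FAAM analysis is adjusted and for what

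*Protocol article*

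**What the plan says.** The relevant statements in the protocol article are these.

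- **Baseline tests** (Statistical analysis): "Independent *t*-tests (*P* <0.05, two-tailed") or a nonparametric alternative "will be used to compare between-group differences in baseline characteristics (Table 1"). Table 1, in the Intervention section, is titled "Baseline measures of participant characteristics". It lists 18 characteristics if treatment preference is counted once, and baseline FAAM, NPRS and EQ-5D are among them.
- **Outcome model** (Statistical analysis): "A repeated measures analysis of variance will be used to compare group differences in the FAAM, NPRS, EQ-5D™, and number of office visits" at each time point. The text does not say whether baseline is one of the repeated levels, and it names no covariate.
- **Adjustment rule** (Statistical analysis): "Analysis of covariance will be used if any group differences are observed in participant characteristics". It does not say which variables then enter, or whether the adjusted model replaces the repeated measures ANOVA or stands beside it.
- **Primary comparison** (Participants): the trial is sized "to detect between-group differences in the primary outcome measure, the FAAM, at 6 months".

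No other part of the article fixes an adjusted analysis.

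**The concern.** Allocation is randomised and concealed, so a baseline difference between the groups is a chance event. Its P value does not show whether the variable predicts the 6-month FAAM. A rule that adjusts only when a difference is seen lets the data choose the model and its covariates. It can bring in a variable unrelated to outcome and leave out baseline FAAM, whose imbalance may matter although it was not flagged.

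Three things are at stake: a primary model that can be stated before the data are seen, the accuracy of the 6-month difference in a trial that happens to be imbalanced, and precision that already-collected baseline data could supply.

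**Working it through.** **Inputs.** From the Participants section: difference 9 points, SD 14.5 (called a variance there but used as an SD, since 9/14.5 = 0.62), alpha 0.05 (taken as two-sided), power 80%, 42 per group raised by 33% to 56. From Table 1: 18 characteristics. Assumed, because the document does not give them: baseline–outcome correlation r of 0.3, 0.5 or 0.7, and a baseline SD of 14.5.

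**1. The plan's own figure.** A two-sample t-test with effect size 9/14.5 has 80.3% power at 42 per group (79.3% at 41), and 42 × 1.33 = 55.9, so 42 and 56 both reproduce. The calculation does not rely on covariate adjustment.

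**2. How often the rule fires by chance**, reading the trigger as P<0.05:

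- 18 independent tests: 1 − 0.95^18 = 0.60
- 10 effective tests: 1 − 0.95^10 = 0.40
- baseline FAAM alone: 0.05

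**3. What an unflagged FAAM imbalance does.** The SE of the baseline difference at 42 per arm is 14.5 × √(2/42) = 3.16 points. An imbalance D with P=0.10 is 1.664 × 3.16 = 5.3 points. An unadjusted 6-month comparison carries r × D. With equal SDs, a change score removes all of D when only r × D was carried forward, which leaves an error of (1 − r) × D in the opposite direction.

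| r | Unadjusted error | Change-score error, opposite direction |
|---|---|---|
| 0.3 | 1.6 points | 3.7 points |
| 0.5 | 2.6 points | 2.6 points |
| 0.7 | 3.7 points | 1.6 points |

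At r=0.5, 2.6 points is 29% of the 9-point target. This is an adverse case. Among trials with baseline P>0.05 the mean absolute imbalance is about 0.72 × 3.16 = 2.3 points, of which about 1.1 is carried at r=0.5 (13% of target). With 56 per arm, P=0.10 corresponds to 4.5 points, and 2.3 are carried at r=0.5 (25%).

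**4. Operating characteristics at 42 per arm.** These come from a simulation of 40,000 trials per setting with one prognostic covariate and one follow-up. The rule is taken to adjust for that covariate only when its own baseline test gives P<0.05. Power for prespecified ANCOVA is from the noncentral t with SD 14.5 × √(1 − r²).

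| Quantity | r=0.3 | r=0.5 | r=0.7 |
|---|---|---|---|
| Power, prespecified ANCOVA | 84% | 90% | 98% |
| Power, conditional rule | 81% | 81% | 82% |
| Power, change score | 66% | 80% | 95% |
| Overall type I error, conditional rule | 4.7% | 4.3% | 3.8% |
| Type I error given baseline P 0.05–0.15, unadjusted | 6.9% | 9.8% | 13.6% |
| Same, change score | 11.3% | 9.7% | 8.7% |
| Same, ANCOVA | 5.1% | 4.7% | 5.1% |

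Relative to an unadjusted comparison, ANCOVA is worth 1/(1 − r²) in sample size: 10%, 33% or 96% more participants.

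**The case against.** The strongest reply has four parts.

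- **The trigger is inferred.** The adjustment sentence says only that differences are observed; the 0.05 level comes from the sentence on baseline tests. This stands as a caution. If 0.05 is not meant, however, the trigger is undefined and leaves more discretion.
- **The repeated measures ANOVA may already use baseline FAAM.** A reader might infer that baseline FAAM is certainly left out. The text does not settle that. If baseline is a level and the group-by-time term is tested, it is handled as a change score. That is a different miscorrection: it beats the unadjusted comparison at r=0.7, ties at r=0.5 and is worse at r=0.3. It does nothing for other characteristics.
- **The size depends on assumptions.** This stands. Entry requires a FAAM ADL score below 74/84, which may reduce both the baseline SD and r, and the point shifts scale with both. The document does not establish which baseline variable predicts outcome best. Imbalances with P between 0.05 and 0.10 arise in only 5% of trials. The 60% is an upper-end figure: height, weight and BMI are correlated, and the symptom scales and expectation items plausibly are too. It is also no measure of harm, because adjusting for an irrelevant variable costs about one degree of freedom.
- **Overall validity is not threatened.** This stands too. A reader might infer that choosing the model from the data inflates false positives, or that the trial is underpowered. Neither is supported: for a single covariate the rule is slightly conservative, and its power is at or above the planned 80%.

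**Conclusion.** The concern holds as a fault in how the model is fixed and as a nearly free improvement passed over. It does not show the trial to be invalid. This is not a detail left to an analysis plan: the article states the rule, and a plan that followed it would inherit the problem.

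At 42 per arm with SD 14.5, prespecified ANCOVA gains about 3, 9 or 16 percentage points of power at r = 0.3, 0.5 or 0.7. An adverse but unflagged FAAM imbalance displaces the 6-month difference by about 1.6 to 3.7 points, in a direction that depends on how baseline enters the ANOVA; a typical one displaces it by about 1 point at r=0.5 if unadjusted. The power gain assumes that a trigger on another variable would not also bring baseline FAAM into the model. The text does not say, and if it did, the gain would be smaller.

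Confidence is high that the rule exists and is data-dependent. The sizes are only as firm as the assumed correlation and baseline SD.

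**What to change.** Replace the conditional sentence with a fixed model. For each outcome measured at baseline (FAAM, NPRS, EQ-5D), model the follow-up values with that outcome's baseline value as a covariate, whatever the observed balance, and do not also enter baseline as a repeated level. Name the 6-month FAAM contrast between groups as primary.

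If further covariates are wanted, fix a short prognostic list now. Symptom duration is a candidate, since the eligibility criteria already treat it as related to poor response. Report Table 1 descriptively and do not use baseline tests to choose covariates.

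The cost is a change of wording and one or two degrees of freedom. The baseline values are already collected, and the sample size need not change.
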